### Recruitment

As part of their recruiting strategy, OzHarvest provides avenues via: media and communications (e.g. *media* releases, word of mouth, school TV shows, and developing and maintaining partnerships with external organizations, such as Nutrition Australia and Sustainable Schools NSW); FEAST promotional activities (e.g. school presentations, parental engagement, video assets, and attending sustainability conferences); as well as digital marketing (e.g. email communications with interested schools). Schools that become interested in the program, register their interest to participate via the OzHarvest web portal [78].

Accordingly, the method of recruitment for this trial has two parts: (a) self-selection by the schools to participate in OzHarvest’s FEAST program in 2021; and (b) invitation by the primary investigator (FK) to the principals of enrolled schools, inviting him/her to allow their school to participate in this trial.

### Assignment of interventions

As this is a pragmatic school-based study, implemented by OzHarvest, randomization will not be possible. The schools self-select to undertake the FEAST program during the school term that best fits in with their academic program, and they also choose whether or not to participate in this trial.

### Blinding (masking)

As with many cluster trials, this trial will be pragmatic in nature as it involves participating in a program in a real-world setting (i.e. primary schools in NSW) and as such, blinding of participants (i.e. students and teachers) will not be possible [79]. However, the biostatistician involved in data analyses will be blinded to group assignment.

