### Trial design

This study will employ a pragmatic approach, involving a parallel, cluster, non-randomized controlled trial (NRCT) with pre- and post-measures. It will involve 20 primary schools (10 intervention vs 10 wait-list control) with children in Grades 5–6, aged 10–12 years, within NSW, Australia. Schools that have self-selected to undertake the FEAST program in 2021 will be invited to participate in this trial.

OzHarvest, a not-for-profit community-based, food-rescue organization, has designed the FEAST program and has been training teachers to implement the program within the classroom setting, in Australian primary-schools, since 2018. The intervention runs for one school term, approximately 10 weeks. Schools participating in the FEAST program during Term 2 (19 April-25 June) of the 2021 scholastic school year will be invited to act as the intervention schools for this trial. Pre- and post-intervention surveys will be issued in the first and last weeks of term, respectively.

Schools participating in the FEAST program during Term 3 (12 July-17 September) and Term 4 (5 October-17 December), will be invited to act as the comparator group (i.e. wait-list control schools). The wait-list control schools will continue with their usual academic programs and will complete the surveys at the same time as the intervention schools (i.e. during the first and last weeks of Term 2). When the wait-list control schools undertake the FEAST program during their chosen school term (Terms 3 or 4), they will be issued with the post-intervention surveys again (third data collection point [T3]), only if they are willing to complete the surveys for their own interest. Previous experience suggests obtaining a third wave of follow-up data from schools is challenging and hence this will not be compulsory. Given variations in the timing of administration and likely low response rates, these data will be used for school feedback only, and not included in the trial.

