OzHarvest provides training, resources and support to teachers to deliver a recommended 1.5-h lesson/week, for a 10-week unit of inquiry (incorporating 10 theory and six practical activities) within the classroom setting. The FEAST program has been integrated with lessons mapped to the Australian Curriculum, embracing Grade 5–6 key learning areas (KLAs) i.e. English [44]; STEM (Science, Technology, Engineering, and Mathematics) curriculum [45]; general capabilities (Literacy, Numeracy, Information and Communication Technologies, Critical and Creative Thinking, Personal and Social Capability and Intercultural Understanding) [46]; and the cross-curriculum priority of sustainability [47]. FEAST has been aligned with the Australian Dietary Guidelines and state/territory-based healthy eating strategies [1], with all recipes including either fruits and/or vegetables (which are also the two most wasted food groups [48]). The program includes a range of educational resources designed to assist in the delivery of the theory and practical components as outlined in Additional file 2 [49]. The lesson plan topics are outlined in Additional file 3 and the practical guide components are outlined in Additional file 4.

Grade 5–6 classroom teachers from the schools that volunteer to participate in the FEAST program, will be invited for a training workshop at OzHarvest offices. A Professional Learning Program will be delivered over six hours of face-to-face training. During the training day, two FEAST education team members will train the teachers in food preparation and cooking skills (making the hot and cold recipes designed for the FEAST program). To assist the teachers and students during the class practical components, teachers will be provided with instructions and resources to seek volunteers throughout the school community such as parents/caregivers, grandparents, and/or school staff etc. Trained volunteers will also be available through OzHarvest, to assist during the practical components. It is recommended that the teachers organize at least one adult per five students, for each of the practical sessions, in addition to themselves.

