##### Implementation (training of teachers, adherence by students and teachers; barriers and facilitators)

Implementation can be defined as the extent to which a program/intervention was delivered as intended, which can be examined at the individual-level and program-level [70]. To monitor adherence/fidelity at the program-level, and to investigate whether teachers delivered the intervention as intended, the post-intervention teacher survey includes questions that ask teachers: what type of training they undertook (face-to-face vs online vs no training); if they implemented the program alone or with another teacher; how many of their students participated in the FEAST program; how many FEAST lessons were conducted; how many cooking sessions were conducted; and if the class created a school cookbook. To monitor adherence at the individual (student level) there is a question embedded within the student post-intervention survey, asking students whether they participated in the cooking activities.

To evaluate whether teachers received all of the resources required to implement the program, embedded within the question to rate the effectiveness of the resources, teachers will also need to ‘tick’ the resources they did not receive.

To gauge potential barriers to implementation, teachers will be asked: if there were any classroom, school or external barriers that impeded students undertaking the FEAST program; whether cost was a barrier to delivering the program; and whether finding volunteers to help with the practical components was an issue.

To gauge potential facilitators, teachers will be asked open-ended questions such as: to describe their favourite aspect of the program; which aspects of the program they thought had the greatest impact on their students; whether they would continue implementing the program and why/why not. Lastly, they will be asked whether they have any feedback, and if they have any suggestions as to how OzHarvest could modify the program in the future.

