### Statistical analysis

Demographic and baseline characteristics will be summarised for both intervention and wait-list control groups and compared for differences at baseline. Standard summary statistics (mean and standard deviation [SD]) or non-parametric statistics (medians and inter-quartile ranges) where applicable, will be used. For the categorical variables, frequencies and percentages will be calculated and reported.

Effects of the intervention on study outcomes will be estimated with generalized linear mixed models (GLMMs) including random intercepts to account for clustering within schools and fixed effects of intervention arm, using appropriate family and link functions according to outcome distribution or type. Models will be adjusted for potential confounders: gender, grade, ICSEA, type of teacher training (face-to-face vs online vs no training), and whether the student speaks another language at home (which will be dichotomized as Yes/No). Analyses will also adjust for baseline levels of the desired outcome. Intracluster correlation coefficients (ICC) for within-school clustering in each intervention effect model will be calculated and reported. Similarly, within-group changes in outcomes will be estimated using GLMMs including random effects for schools and individuals, and fixed effects of time. Estimated intervention effects and within-group changes will be reported as unstandardized regression coefficients or exponentiated coefficients (e.g. odds ratios), with 95% confidence intervals and *p*-values.

All analyses will follow the intention-to-treat (ITT) principles and missing data will be handled using multiple imputation by chained equations [80]. Imputation of outcome variables (and covariates if missing) will be conducted separately by intervention group and will include schools and covariates as auxiliary variables [80].

To assess sensitivity of the findings to different assumptions around the missing data mechanism, complete case analyses (valid under a missing completely at random assumption) will also be conducted as a sensitivity analysis. No interim analyses of trial outcomes are planned nor any stopping rules.

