The strengths of the evaluation design include the use of: the 33-item SPIRIT checklist to guide the design of the protocol; using a controlled design; questions for the primary outcomes derived from reliable and validated measures tested on this age group; many of the secondary outcomes, were also derived from reliable and validated measures. The trial is well powered to detect changes in outcomes and the trial statistician will be blinded to group allocation when conducting the statistical analyses. Also, this trial has included qualitative questions embedded within the quantitative surveys. The combination of qualitative and quantitative components within the surveys, will enable the trial’s conclusions to be expanded upon [87, 88]. If triangulation of results is found between qualitative and quantitative components, then convergence of outcomes allows for stronger inferences about findings [87, 88].

Furthermore, non-randomized evaluation designs can contribute data on the effectiveness of interventions, and if conducted and reported systematically, have the capacity to contribute to building evidence-based public health practices [89]. Accordingly, the TREND (Transparent Reporting of Evaluations with Nonrandomized Designs) [89] and the CONSORT (Consolidated Standards of Reporting Trials) statement for pragmatic trials [90] will be used to report outcomes.

Given the challenges of promoting healthy diets, sustainable eating and reducing food waste at the population level, the FEAST program is well-positioned to play a key role in this school-based approach to engage students to eat healthily and sustainably. Initiatives undertaken within the school system have the added advantage of reaching large, diverse populations, placing them in a unique situation to deliver universal and equitable public health strategies [11, 23, 33].

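### The statistician is declared blind to group, but the planned models need a teacher-training covariate that would reveal which group is FEAST if wait-list teachers are untrained at T2

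*Protocol article*

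**What the plan says.** Under Blinding (masking), the protocol article says that students and teachers cannot be blinded, then adds: "However, the biostatistician involved in data analyses will be blinded to group assignment". The Discussion repeats this as a strength: "the trial statistician will be blinded to group allocation when conducting the statistical analyses". Neither statement is qualified.

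Under Statistical analysis, the covariates for the effect models are fixed: "Models will be adjusted for potential confounders: gender, grade, ICSEA, type of teacher training (face-to-face vs online vs no training"), plus home language and the baseline value of the outcome.

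The training variable belongs to FEAST delivery. Under Intervention, "OzHarvest provides training, resources and support to teachers to deliver a recommended 1.5-h lesson/week, for a 10-week unit of inquiry". Under Implementation, it is among the fidelity questions in the post-intervention teacher survey: "what type of training they undertook (face-to-face vs online vs no training); if they implemented the program alone or with another teacher". Under Trial design, "The wait-list control schools will continue with their usual academic programs and will complete the surveys at the same time as the intervention schools", and data collected after the wait-list schools' own FEAST term are kept out of the trial.

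**The concern.** The article fixes two things that sit badly together. The analyst is not to know the arms, yet cannot fit the stated models without a field describing how a teacher was prepared to deliver the intervention. Coding the arms as A and B gives no protection if that field shows training in one group and none in the other.

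The schools choose their own term, nobody in the classroom is blinded, and the outcomes are children's self-reports. Analyst blinding is the only masking described. A results paper that followed the article would report this safeguard although it may have lapsed once the covariate was tabulated.

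**Working it through.** There is no stated figure to reproduce. The check has two parts: reading the sections against each other, and counting how far the covariate gives the arm away.

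**Reading the sections together**

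1. The analyst must hold training type for each student, because it is in the model (Statistical analysis).
2. It records FEAST training (Intervention; Implementation).
3. Wait-list schools do not run FEAST before T2, and their later FEAST-term data are excluded (Trial design). On the natural reading, their value is no training, or blank if their teachers are not asked.
4. FEAST schools should mostly show in-person or online training.
5. The article describes no step that keeps this field from the analyst.

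**Counting**

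Inputs: 10 FEAST and 10 wait-list schools (Trial design). Assumptions: all teachers in a school have the same training status, and any training is compared with none. Let *a* be the number of FEAST schools trained and *b* the number of wait-list schools trained by T2. Neither is given, so a range is shown.

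- Schools classified correctly by the rule that a trained school is a FEAST school: *a* + (10 − *b*), out of 20.
- Squared correlation of training with arm: R² = [*a*(10 − *b*) − *b*(10 − *a*)]² / [10 × 10 × (*a* + *b*) × (20 − *a* − *b*)].
- Variance inflation from these two variables alone: VIF = 1/(1 − R²).

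| *a* | *b* | Schools read correctly | R² | VIF |
|---|---|---|---|---|
| 10 | 0 | 20/20 | 1.000 | infinite |
| 9 | 0 | 19/20 | 0.818 | 5.5 |
| 8 | 0 | 18/20 | 0.667 | 3.0 |
| 10 | 1 | 19/20 | 0.818 | 5.5 |
| 10 | 2 | 18/20 | 0.667 | 3.0 |
| 10 | 5 | 15/20 | 0.333 | 1.5 |
| 10 | 10 | 10/20 (no information) | undefined | undefined |

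Example for *a* = 10, *b* = 1: correct = 10 + 9 = 19; R² = (10 × 9 − 1 × 0)² / (100 × 11 × 9) = 8100/9900 = 0.818; VIF = 1/(1 − 0.818) = 5.5.

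With an A/B code in the file, the analyst needs only the majority pattern. Counts of 10 against 0, 8 against 0 or 10 against 2 all point to the same group. The covariate says nothing only in the last row.

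**The case against.** **Masking procedures may be described elsewhere.** Who prepares the file, and when fields are released, normally belongs in an analysis or data-management plan that is not shown. That is fair, and the absence of such detail is not the point. The point is that the blinding claim and the covariate list are both stated here, and a plan that implemented both faithfully would inherit the conflict. The Data management section's de-identification of school data serves confidentiality; it does not remove a covariate the model needs.

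**The training status of wait-list teachers at T2 is not given.** This stands and makes the finding conditional. These schools are already registered for FEAST in 2021. Term 2 ends on 25 June and Term 3 starts on 12 July, 17 days later, so some Term 3 teachers could be trained before T2. The no-training answer is also open to a teacher who delivered FEAST untrained, so it does not mark a control by definition. A reader might infer that the blind cannot possibly hold; the document does not support that much.

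**Other suspected leaks are weaker.** A reader might infer that the cooking question also unmasks the arms, since "there is a question embedded within the student post-intervention survey, asking students whether they participated in the cooking activities". That item is process data, analysed descriptively and used in no effect model, so it can be kept from the analyst. A reader might also suspect ICSEA, because it is published by school. At most it suggests a school's identity; the arm follows only if one knows which term that school chose. Imputing separately by group needs only masked codes.

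**Blinding is not presented as the guard on modelling choices.** This also stands. The Discussion's named protections against bias are a detailed protocol and pre-specified analysis, with analyst blinding listed separately as one strength. Nothing ties it to the choice of link function, summary statistics or imputation model.

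**Conclusion.** The concern holds in conditional form. If wait-list teachers are untrained at T2, the training covariate shows which coded group is FEAST, and the blind claimed in the Blinding section and the Discussion would not survive the planned analysis. The arm of 20 of 20 schools is then readable, or of 18 to 19 with one or two exceptions in either arm. If half the wait-list schools were trained it would be 15 of 20, and if all were trained the covariate would reveal nothing.

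This rests on the control value being inferred from the design and on training status being uniform within schools. The consequence is for the credibility of a stated safeguard. No effect on sample size, alpha or power is shown, and analyst blinding would not remove the biases from self-selection and self-report that the article acknowledges. It should be corrected before analysis, but it does not invalidate the trial.

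**What to change.** Take training type out of the primary and secondary effect models. It is part of the intervention and, on the natural reading, close to collinear with arm, so little adjustment is lost: in the 20-of-20 case its any-versus-none contrast cannot be separated from the intervention effect at all.

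Have someone outside the analysis prepare a file with arm coded A/B. Withhold training type and the FEAST-only process items until the primary and secondary models are locked. Then release them and examine training type openly, for example within FEAST schools.

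The cost is a declared change to the prespecified covariate list and a two-stage data release. It is more than a data-preparation step, because the primary model changes, and the amendment should say so.

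If training type is to stay in the models, qualify or withdraw the blinding claim in both the Blinding section and the Discussion. Either way, state what value of training type wait-list classes take at T2.

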### Data collection methods

The class teachers participating in the FEAST trial, will receive a URL link to access student surveys, on the REDcap platform, in the last week of the school term preceding implementation. The teacher will then email this link to his/her entire class in week one of the school term, that FEAST will be implemented. At the end of the school term, a second URL link will be issued to the class teachers to access the post-FEAST survey. The teachers will set up a time for all students in their class to complete the pre-FEAST survey prior to starting the program (T1) and the post-FEAST surveys on program completion (T2). Schools acting as the wait-list controls will also complete the surveys at the same time as intervention schools (i.e. at T1 and T2). The PI (FK) and/or OzHarvest volunteers will assist the teachers in data collection (subject to COVID19 regulations).

### Data management

Data will be stored securely as per the requirements of the Deakin University, Human Ethics Advisory Groups for the Faculty of Health. Data will only be accessible to the research team and trial biostatistician. Confidential participant (student and teacher) and school data, will be deidentified and stored securely and will not be linked to survey responses.

### Statistical analysis

Demographic and baseline characteristics will be summarised for both intervention and wait-list control groups and compared for differences at baseline. Standard summary statistics (mean and standard deviation [SD]) or non-parametric statistics (medians and inter-quartile ranges) where applicable, will be used. For the categorical variables, frequencies and percentages will be calculated and reported.

Effects of the intervention on study outcomes will be estimated with generalized linear mixed models (GLMMs) including random intercepts to account for clustering within schools and fixed effects of intervention arm, using appropriate family and link functions according to outcome distribution or type. Models will be adjusted for potential confounders: gender, grade, ICSEA, type of teacher training (face-to-face vs online vs no training), and whether the student speaks another language at home (which will be dichotomized as Yes/No). Analyses will also adjust for baseline levels of the desired outcome. Intracluster correlation coefficients (ICC) for within-school clustering in each intervention effect model will be calculated and reported. Similarly, within-group changes in outcomes will be estimated using GLMMs including random effects for schools and individuals, and fixed effects of time. Estimated intervention effects and within-group changes will be reported as unstandardized regression coefficients or exponentiated coefficients (e.g. odds ratios), with 95% confidence intervals and *p*-values.

All analyses will follow the intention-to-treat (ITT) principles and missing data will be handled using multiple imputation by chained equations [80]. Imputation of outcome variables (and covariates if missing) will be conducted separately by intervention group and will include schools and covariates as auxiliary variables [80].

To assess sensitivity of the findings to different assumptions around the missing data mechanism, complete case analyses (valid under a missing completely at random assumption) will also be conducted as a sensitivity analysis. No interim analyses of trial outcomes are planned nor any stopping rules.

Analyses for the process evaluation, involving responses from students and teachers, will involve descriptive statistics for the quantitative component using standard summary statistics. While the qualitative component, which involves responses to open-ended questions, will be analysed using both content and thematic analyses, as well as qualitative description [81, 82].

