A 3-h NESA accredited online teacher training version of the FEAST program was developed for schools in regional and remote areas of NSW (as defined in the *‘school facts location identified’*), which is published on the *MySchool* website [50]. This can also be used by teachers that are unable to attend the 6-h face-to-face training, due to additional circumstances, including COVID19 restrictions.

The teachers using the online training have the option to work through the training module at their own pace. Teacher instructions on how to use the online learning resources and adapt them to their students’ needs have also been included in the online training module. Lesson plans; how to conduct the practical cooking sessions with instructional videos on good cooking techniques for making some of the recipes at home, including parent roles; and access to all of the same resources as the face-to-face training are available through the online module. Email and phone support from the FEAST education team will also be available to the teachers undertaking the online training. The online training will also be used in the event that COVID19 restrictions prevent face-to-face training in 2021.

Strategies to improve adherence to the FEAST program include: accredited teacher training program; a complete curriculum package for the teachers; lessons plans mapped to the Australian Curriculum, KLAs (English and STEM), general capabilities, and cross-curriculum priority area of sustainability; activity booklets for students with answer booklets for teachers; training of OzHarvest volunteers to assist in the practical activities (subject to COVID19 regulations); as well as open communication (phone and/or email) between the FEAST education team and teachers during implementation, to provide support.

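### The between-arm effect models adjust for type of teacher training, a component of FEAST, so the arm coefficient does not estimate the effect of the whole program and may not be estimable

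*Protocol article*

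**What the plan says.** The Statistical analysis section specifies generalized linear mixed models with "random intercepts to account for clustering within schools and fixed effects of intervention arm". It then lists the covariates for those models: "Models will be adjusted for potential confounders: gender, grade, ICSEA, type of teacher training (face-to-face vs online vs no training"). Language spoken at home and the baseline value of the outcome are added. The adjustment is not limited to the intervention arm. The same section commits all analyses to intention-to-treat principles and imputes missing data separately by group.

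Three other statements describe what training is:

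- Intervention section: "OzHarvest provides training, resources and support to teachers to deliver a recommended 1.5-h lesson/week, for a 10-week unit of inquiry".
- Intervention section, on adherence: "Strategies to improve adherence to the FEAST program include: accredited teacher training program".
- Implementation subsection of the process evaluation, on monitoring fidelity: "the post-intervention teacher survey includes questions that ask teachers: what type of training they undertook (face-to-face vs online vs no training").

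On the comparator, the Trial design section says: "The wait-list control schools will continue with their usual academic programs". These schools take up FEAST in Term 3 or 4. The text does not state when their teachers are trained or how the training variable is coded for them.

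**The concern.** A confounder is a cause of the outcome that also influences, or shares a cause with, the exposure. Teacher training is instead one of the things a school receives by being in the intervention arm. Holding it fixed while comparing arms asks what FEAST does apart from its training. The primary objective asks about the program as delivered.

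There is also an identification problem. If training occurs only in one arm, the training indicators and the arm indicator carry nearly the same information. The model then has little or nothing left from which to estimate the arm effect. The covariate sentence governs both primary outcomes and every secondary between-arm model, so the trial's main conclusions depend on it.

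**Working it through.** **Inputs.** From the Sample size section: 10 schools per arm, mean cluster size m = 50 with CV 0.436, ICC 0.04, baseline to follow-up correlation 0.5, SD 1.3 (vegetables) and 1.1 (fruit), difference 0.5 serves/day, alpha 0.025, 20% loss. Assumptions made here: alpha is two-sided, and 50 is students per school. The text says per arm, but the stated power reproduces only with 50 per school.

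**Step 1: reproduce the stated power (90% and 97%).**
Design effect = 1 + ((CV² + 1)m − 1) × ICC. SE = SD × √(2 × (1 − 0.5²) × design effect / (10m)).

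- m = 50: design effect 1 + (1.190 × 50 − 1) × 0.04 = 3.34. SE 0.130 and 0.110. Power (noncentral t, 18 df) 90.7% and 97.6%.
- m = 40 (after 20% loss): design effect 2.864. SE 0.135 and 0.114. Power 88.6% and 96.6%.

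The plan's figures are reproduced within 2 points, and they belong to a model without training.

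**Step 2: all controls coded as untrained, all intervention schools trained.**
At school level the columns are intercept, arm, face-to-face and online. Arm = face-to-face + online in every row. With 5 face-to-face and 5 online intervention schools the matrix has rank 3 for 4 columns, so there is no unique arm coefficient. Software would drop a term, and the choice of term would decide what is reported as the effect.

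**Step 3: controls untrained, k of 10 intervention schools untrained.**
The trained schools all lie in one arm and are absorbed by their own indicators. Only the k untrained schools are compared with the 10 controls:

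SE ratio = √((1/k + 1/10) / (2/10)).

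- k = 1: √(1.1/0.2) = 2.35
- k = 2: √(0.6/0.2) = 1.73

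Power with m = 40 and 16 df (20 schools less 4 parameters, other covariates ignored):

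| Model | SE veg / fruit | Power veg | Power fruit |
|---|---|---|---|
| Reference SE, same 16 df | 0.135 / 0.114 | 88% | 96% |
| Training included, k = 1 | 0.316 / 0.267 | 22% | 30% |
| Training included, k = 2 | 0.233 / 0.197 | 40% | 54% |

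**Step 4: what the coefficient then estimates.**
Take k = 2, a true effect of 0.5 in trained schools and u in untrained schools. The adjusted arm coefficient is u. Without training in the model it is (8 × 0.5 + 2u)/10.

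| u | Adjusted for training | Not adjusted |
|---|---|---|
| 0 | 0 | 0.40 |
| 0.25 | 0.25 | 0.45 |
| 0.5 | 0.5 | 0.50 |

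**Step 5: untrained classes spread over schools.**
Training is asked of each teacher. Assume two classes of 20 per school and no class-level variance. Two untrained classes in different schools give an SE ratio of 1.83, against 2.35 when both are in one school. Four spread over four schools give 1.41, against 1.73. Applied to the vegetable SE of 0.135, these ratios give about 0.246 and 0.190, and power of about 36% and 57% (16 df).

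**Step 6: some controls already trained.**
Suppose controls are 3 face-to-face, 2 online and 5 untrained, and intervention schools are 5 and 5. The arm effect now comes only from comparisons within training mode. The variances are 1/5 + 1/3 = 0.533 and 1/5 + 1/2 = 0.700. Combined variance is 1/(1/0.533 + 1/0.700) = 0.303, against 0.2 without training, a ratio of 1.51. Power is about 70% and 85% (16 df), or 78% and 91% by the normal approximation. The five untrained control schools contribute nothing to the contrast. With a 5/5 mix in both arms the ratio is 1.0 and nothing is lost.

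**The case against.** The strongest reply is that exact aliasing is not established. A reader might infer that the arm effect is bound to be inestimable. The article does not support that. Control schools are already registered for FEAST in 2021, their teachers administer the surveys in Term 2, and the Intervention section links teacher training with learning the survey platform. Some control teachers could therefore be trained before the second survey. Continuing usual academic programs describes what pupils are taught, not teachers' training status, and the timeline figure is not available here. This stands, so non-estimability and the power losses are conditional.

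It also stands that the training mix is unknown, that Step 3 treats training as a whole-school attribute, and that the loss is smaller if untrained classes are scattered.

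The authors had a visible reason to think of training mode: it depends partly on a school's location, which precedes the trial. The objection to the covariate should also not rest on its being recorded after the intervention, because training itself comes before delivery. The sound objection is that training belongs to the package.

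Two further inferences go too far. One is that the covariate breaks the promise that "the biostatistician involved in data analyses will be blinded to group assignment". That depends on the same unstated control coding and adds nothing to the main point. The other is that training must leave the imputation models. Imputation is done separately by group, so training cannot be aliased with arm there.

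None of this makes the covariate suitable for the between-arm model. Nor can it be left to another document, since the Discussion says the pre-specified analysis plan is included in this article.

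**Conclusion.** The point holds. As written, the between-arm models condition on a component of the intervention. The arm coefficient therefore no longer estimates the effect of the whole FEAST program, which conflicts with the intention-to-treat commitment. This conclusion rests on the text alone.

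The numerical damage depends on facts the article does not give. It ranges from none (training mix balanced across arms), through a variance about 1.5 times larger (half the control schools trained), to a standard error 1.73 to 2.35 times larger with two or one untrained intervention schools and all controls untrained. At the far end the arm effect is not estimable (all controls untrained, all intervention teachers trained). The power figures assume the article's sample size inputs, 40 students analysed per school, two-sided alpha of 0.025 and 16 df.

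**What to change.** Remove type of teacher training from the covariate list of all between-arm intervention-effect models, primary and secondary. Keep it as an implementation descriptor, and explore outcomes by training type only within the intervention arm. It may stay in the arm-specific imputation models, and no replacement covariate is needed.

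The change should be made before outcome data are analysed, because deciding later which aliased term to drop would be a data-dependent choice. It costs one sentence, with no effect on data collection or recruitment. It frees two school-level degrees of freedom (18 rather than 16 in the working above) and restores the model on which the stated power of 90% and 97% rests.
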